## Methods/design

This is a prospective, randomised, double-blind, placebo-controlled trial to assess the feasibility of undertaking a definitive trial investigating the efficacy of baclofen in treating GHB/GBL withdrawal, both in planned and unplanned withdrawal using both quantitative and qualitative approaches. The optimal recruitment rate and strategies and characteristics of the proposed primary outcome measures (symptom severity, complications, and requirement for treatment escalation) will be assessed. Ethical approval has been obtained from National Research Ethics Service Committee London – Dulwich and the EUDRACT number is 2013-005319-28.

### Research settings

The study will recruit from two services where individuals present for treatment of GHB/GBL withdrawal. The CNWL Club Drug Clinic, based in Central London, UK is an outpatient clinic where individuals are referred or self-present for treatment for GHB/GBL dependence and may undergo planned detoxification as part of their treatment package, and secondly, to a specialist Clinical Toxicology Service at Guy’s and St. Thomas’ NHS Foundation Trust, London, UK for those who present with unplanned withdrawal requiring immediate management. For planned detoxification group recruitment, we have produced a trial poster and short information sheet for use at our linked clinical services to ensure an adequate appropriate recruitment rate. We will display this poster at such clinical services and staff will be encouraged to provide a copy of the short information sheet for planned withdrawal.

### Participants

#### Inclusion criteria

Any individual who is over 18 years old, is either in active GHB/GBL withdrawal or has underlying GHB/GBL dependence and wishes to undergo GHB/GBL detoxification or is thought to have underlying GHB/GBL dependence and is at risk of acute withdrawal and, for the outpatient arm only, who is registered with a drug treatment service, will be eligible for the study.

#### Exclusion criteria

An individual will not be eligible for inclusion in this study if they are unable to provide written informed consent and any of the following criteria apply: the clinician decides that medication is not required for the management of GHB/GBL withdrawal; if medication is indicated but the patient lacks capacity to consent, is unable to take oral medication or is unable to take baclofen according to SPC due to known hypersensitivity to baclofen or any of the excipients, hereditary problems of galactose intolerance, the Lapp lactase deficiency or glucose-galactose malabsorption, active peptic ulceration or porphyria. In addition, for those with epilepsy that is not well-controlled, either with or without medication, or those with end-stage renal failure (Chronic Kidney Disease (CKD) stage 5, GFR below 15 mL/min) (which have special warnings and precautions for use, according to the SPC) will not be entered since the risk versus benefit ratio for prescribing is not in favour of prescribing baclofen. In addition, participants who are unable to follow the study protocol due to serious mental health disorder, e.g. enduring psychotic illness or suicidal intent will not be eligible. Further, any participant who has taken any investigational drug within 30 days prior to drug administration or any woman refusing a pregnancy test will not be eligible.

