### Randomisation

An assessment of eligibility will be made by a physician following discussion with the potential participant and review of the accessible medical records. For some participants wishing to participate in the study but where there is limited or no access to medical records, the individual will be included in the trial unless one or more of the eligibility criteria are known not to be met. Informed consent will be obtained by a member of the study team.

To be able to respond to the urgent needs of people who are at high risk of withdrawing from GHB/GBL in a timely manner, the study medication will be pre-packed and pre-randomised and stored at both study sites. Randomisation codes in blocks of 4 (for the planned withdrawal group) and blocks of 15 (for the unplanned withdrawal group) will be generated by the trial statistician. Those eligible for inclusion will be randomised to baclofen or placebo by taking the next lowest consecutively numbered pack from storage cupboards in the respective treatment centre.

If eligible, have given informed consent and following baseline assessment, the participants are allocated as follows (see Fig. 1a and b). Those in the planned arm will receive a preload before their detoxification proper and will be allocated to one of three groups: preload of placebo (one tablet three times a day) followed by the benzodiazepine GHB/GBL detoxification regimen with the study medication, baclofen (10 mg three times a day) or placebo (one tablet three times a day) for up to 10 days, or preload of baclofen (10 mg three times a day) followed by the benzodiazepine GHB/GBL detoxification regimen with baclofen (10 mg three times a day) for up to 10 days. Those in the unplanned arm will receive their benzodiazepine detoxification regimen for GHB/GBL withdrawal with the study medication, baclofen (10 mg three times a day) or placebo (one tablet three times a day) for up to 10 days. In both unplanned and planned GHB/GBL withdrawal, clinicians will use the benzodiazepine and dosing regimen that they consider appropriate. The study medication will be discontinued at the same time as the benzodiazepine, with the decision about when both medications are to be discontinued made by their clinician.

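### The first exclusion sentence is joined by 'and', so read literally its listed items do not exclude a patient who can consent

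*Protocol article*

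**What the plan says.** The Exclusion criteria section of the protocol article has four sentences.

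The first opens with a joint condition: a person is ineligible "if they are unable to provide written informed consent and any of the following criteria apply". The items after the colon are:
- a clinical judgement that the withdrawal needs no drug treatment;
- lack of capacity in someone who does need treatment, worded as "if medication is indicated but the patient lacks capacity to consent";
- being unsuitable for oral treatment or for the study drug. The list of reasons for the latter starts with hypersensitivity to baclofen or its excipients and also names galactose intolerance, Lapp lactase deficiency, glucose-galactose malabsorption, active peptic ulceration and porphyria.

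The other three sentences do not mention consent:
- The second begins "In addition, for those with epilepsy that is not well-controlled, either with or without medication, or those with end-stage renal failure" and concludes that such people "will not be entered since the risk versus benefit ratio for prescribing is not in favour of prescribing baclofen".
- The third excludes those whose serious mental health disorder prevents them from following the protocol.
- The fourth excludes anyone given an investigational drug in the preceding 30 days, and adds that "any woman refusing a pregnancy test will not be eligible".

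The Randomisation section says that a physician assesses eligibility, that the study team obtains informed consent, and that only eligible people who have consented are allocated. For people with few or no accessible records, "the individual will be included in the trial unless one or more of the eligibility criteria are known not to be met".

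**The concern.** In an exclusion list, each item should normally be sufficient to keep a person out. Here the opening clause makes inability to consent a necessary part of every exclusion in the first sentence. Nobody can be randomised without consent, so the clause disables the list it introduces.

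The items affected include the document's own reasons, taken from the product characteristics, why some people should not receive baclofen. The wording of the eligibility section also decides who counts as an eligible participant and what counts as a protocol deviation, and deviations are recorded under Table 1. Someone with a listed contraindication who consents and is randomised would, on the literal text, be correctly enrolled and would not be a deviation.

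**Working it through.** No arithmetic applies, and the plan gives no figure to reproduce. The check is one of logic.

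**Inputs**
- C: the person can give written informed consent. The Randomisation section requires consent before allocation.
- L: at least one item in the list of the first exclusion sentence holds.
- S: at least one ground in the second to fourth exclusion sentences holds (epilepsy not well controlled, CKD stage 5, serious mental disorder, recent investigational drug, refused pregnancy test).

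**Rule as written:** excluded if (not C *and* L) *or* S.

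**Rule with each criterion acting alone:** excluded if (not C) *or* L *or* S.

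**Cases for the first sentence, with S false**

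| Can consent | Listed item present | First sentence as written | Criteria acting singly |
|---|---|---|---|
| Yes | No | not excluded | not excluded |
| Yes | Yes | not excluded | excluded |
| No | No | not excluded by this sentence | excluded |
| No | Yes | excluded | excluded |

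The two readings differ in the second and third rows. The third does no damage, because the Randomisation section separately requires consent. The second is the defect: for example, a consenting person with known hypersensitivity to baclofen, active peptic ulceration or porphyria is not excluded.

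**Cases with S true:** the person is excluded under both rules, whether or not they can consent. The defect stops at the first sentence.

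**Is the conjunction intended?** Two comparisons say not.
1. Lack of capacity to consent is itself an item in the list. Under *and*, that item largely repeats the condition that governs it. It makes sense only if the items were meant to stand alone.
2. The Randomisation section keeps a person out once a single criterion is known to fail. That is the logic of separate criteria and does not fit the joint condition.

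**The case against.** The best defence is that the meaning is plain in context. The sentence can be read as saying that people who cannot consent are ineligible, and that people to whom any item applies are ineligible too. The contraindications are named, the next sentence adds further grounds with *In addition*, and a physician assesses eligibility. A physician is unlikely to take the sentence as permission to enrol someone known to be hypersensitive to baclofen. Much of this stands: it limits the likely practical harm and confirms what was meant. It does not make the written rule correct. Nor is this detail that an article leaves to the full protocol, because the rule is present and is stated wrongly.

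Three stronger readings are tempting, and the document does not support them.
- *That no exclusion works for a consenting patient.* The second to fourth sentences exclude without any reference to consent.
- *That nothing else would stop these patients.* The physician's assessment applies to everyone. Lack of capacity is caught by the consent requirement. People who need no medication or cannot take it by mouth are largely caught by the design, which gives tablets alongside a benzodiazepine regimen. The default to inclusion covers only people with limited or no records, and its single-criterion wording supports the intended reading. What remains exposed on the literal text is mainly the set of product-characteristics contraindications.
- *That the pregnancy test has no effect because no consequence of a positive result is given.* That is an inference from silence. A condensed article may leave this to the full protocol, so it is not part of this point.

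**Conclusion.** The point holds for the first exclusion sentence only. As written, none of its items excludes a patient who can consent, and this conflicts both with the sentence's own list and with the Randomisation section. This follows from the wording and says nothing about how many patients would be wrongly enrolled. That number is probably small, because the intent is fairly evident and a physician checks eligibility.

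The conclusion assumes that the article reproduces the operative wording of the protocol. If the full protocol already lists the criteria separately, only the article needs correcting. The matter is a low-cost correction of an eligibility rule that bears on patient safety. It changes no sample size, alpha or power figure.

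**What to change.** In the first exclusion sentence, replace the joining *and* with *or if any one*, so that inability to consent and each listed item are separate and sufficient grounds. Set every criterion out as its own numbered exclusion, including those now in the second to fourth sentences, and remove the overlap between inability to consent and lack of capacity. Then check the result against the Randomisation section so that both apply the criteria singly. The clinical content of the list stays with the investigators.

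The cost is a wording change in the eligibility section and in any screening form copied from it. Design, sample size and analysis stay as they are.

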### Randomisation

An assessment of eligibility will be made by a physician following discussion with the potential participant and review of the accessible medical records. For some participants wishing to participate in the study but where there is limited or no access to medical records, the individual will be included in the trial unless one or more of the eligibility criteria are known not to be met. Informed consent will be obtained by a member of the study team.

To be able to respond to the urgent needs of people who are at high risk of withdrawing from GHB/GBL in a timely manner, the study medication will be pre-packed and pre-randomised and stored at both study sites. Randomisation codes in blocks of 4 (for the planned withdrawal group) and blocks of 15 (for the unplanned withdrawal group) will be generated by the trial statistician. Those eligible for inclusion will be randomised to baclofen or placebo by taking the next lowest consecutively numbered pack from storage cupboards in the respective treatment centre.

If eligible, have given informed consent and following baseline assessment, the participants are allocated as follows (see Fig. 1a and b). Those in the planned arm will receive a preload before their detoxification proper and will be allocated to one of three groups: preload of placebo (one tablet three times a day) followed by the benzodiazepine GHB/GBL detoxification regimen with the study medication, baclofen (10 mg three times a day) or placebo (one tablet three times a day) for up to 10 days, or preload of baclofen (10 mg three times a day) followed by the benzodiazepine GHB/GBL detoxification regimen with baclofen (10 mg three times a day) for up to 10 days. Those in the unplanned arm will receive their benzodiazepine detoxification regimen for GHB/GBL withdrawal with the study medication, baclofen (10 mg three times a day) or placebo (one tablet three times a day) for up to 10 days. In both unplanned and planned GHB/GBL withdrawal, clinicians will use the benzodiazepine and dosing regimen that they consider appropriate. The study medication will be discontinued at the same time as the benzodiazepine, with the decision about when both medications are to be discontinued made by their clinician.

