**Fig. 1 Fig1:**
[figure not shown]
**a** CNWL Club Drug Clinic – Planned (outpatient) withdrawal, *N* = 60 (three groups). **b** GSTT clinical toxicology service – Unplanned (inpatient) withdrawal, *N* = 28 (two groups). *CNWL* Central North West London NHS Foundation Trust, *GSTT* Guy’s and St. Thomas’s NHS Foundation Trust

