### Sample size

The aim is to recruit 88 research participants who are undergoing GHB/GBL detoxification: 60 planned outpatients and 28 unplanned inpatients.

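### The stated randomisation block sizes do not fit the number of arms in either group, and are very probably transposed

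*Protocol article*

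**What the plan says.** The Randomisation section of the protocol article fixes one block size per group: "Randomisation codes in blocks of 4 (for the planned withdrawal group) and blocks of 15 (for the unplanned withdrawal group) will be generated". The same section sets out the arms. For the planned group: "Those in the planned arm will receive a preload before their detoxification proper and will be allocated to one of three groups". These are placebo preload then placebo, placebo preload then baclofen, and baclofen preload then baclofen. For the unplanned group: "Those in the unplanned arm will receive their benzodiazepine detoxification regimen for GHB/GBL withdrawal with the study medication, baclofen (10 mg three times a day)". The comparator there is placebo, which makes two arms. The Fig. 1 legend agrees, giving "Planned (outpatient) withdrawal, *N* = 60 (three groups") for the outpatient setting and two groups with N = 28 for the inpatient setting. The Sample size section repeats the totals: "60 planned outpatients and 28 unplanned inpatients".

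No allocation ratio appears in the text. The Randomisation section refers the reader to Fig. 1, which is not reproduced in the copy reviewed.

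**The concern.** A permuted block balances the arms only if its size is a multiple of the number of arms (or of the sum of the ratio terms, if allocation is unequal). The article attaches the size that suits two arms to the three-arm group, and the size that suits three arms to the two-arm group.

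This is a stated allocation rule that does not fit the stated design, so it is not a detail left to another document. It matters because study packs are numbered and randomised in advance and each site takes the next one in sequence. Any error in the list would become the allocation, and packs already used cannot be re-randomised. Unintended unequal arms would also change the meaning of the safety trigger in the Data analysis section, which counts five escalations in any one group. Five events are 5/20 = 25% of an arm of 20, but 5/30 = 17% of an arm of 30 and 5/15 = 33% of an arm of 15.

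**Working it through.** **Inputs.** Block sizes 4 (planned) and 15 (unplanned): Randomisation section. Arms 3 and 2: Randomisation section and Fig. 1 legend. N = 60 and 28: Sample size section and Fig. 1 legend. Assumption: equal allocation, that is 20 per planned arm and 14 per unplanned arm.

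**Divisibility.** Equal arms within a block need block size mod number of arms = 0. Ending on a complete block needs N mod block size = 0.

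| Group | Arms | N | Block | Per arm per block | Block mod arms | N / block |
|---|---|---|---|---|---|---|
| Planned, as printed | 3 | 60 | 4 | 1.33 | 1 | 15, remainder 0 |
| Unplanned, as printed | 2 | 28 | 15 | 7.5 | 1 | 1, remainder 13 |
| Planned, exchanged | 3 | 60 | 15 | 5 | 0 | 4, remainder 0 |
| Unplanned, exchanged | 2 | 28 | 4 | 2 | 0 | 7, remainder 0 |

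As printed, the arms do not divide the block in either group. Exchanged, all four divisions are exact: 4 × (5:5:5) = 20:20:20 and 7 × (2:2) = 14:14.

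**Size if used as printed, planned group.** The only split of 4 with all three arms present is of the 2:1:1 type. With the same arm doubled every time, 15 blocks give 30:15:15. The standard error of a difference is proportional to √(1/n₁ + 1/n₂):

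- 20 v 20: √(2/20) = 0.316.
- 15 v 15: √(2/15) = 0.365; ratio 0.365/0.316 = 1.155, a rise of 15%.
- 30 v 15: √(1/30 + 1/15) = √0.1 = 0.316; ratio 1.00, no loss.

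The preload comparison (placebo preload v baclofen preload, both followed by baclofen) loses precision only if the doubled arm is the third one, placebo throughout.

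**Size if used as printed, unplanned group.** The nearest split of 15 is 8:7. Take each block as 8:7 or 7:8 with equal chance. The 28 participants use all of block 1 and 13 codes of block 2, so two codes of block 2 stay unused. There are C(15,2) = 105 possible unused pairs: 28 with both from the arm of eight, 56 with one from each arm, and 21 with both from the arm of seven.

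- Both blocks favour the same arm: 14:14 in 28/105, 15:13 in 56/105, 16:12 in 21/105 (27%, 53%, 20%).
- Blocks favour opposite arms: 14:14 in 56/105, a difference of 2 in (28 + 21)/105 = 49/105 (53%, 47%), and never 16:12.
- Averaged: 14:14 in 84/210 = 40%, a difference of 2 in 105/210 = 50%, 16:12 in 21/210 = 10%.

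The arms are therefore unequal in 60% of runs, and 16:12 is the largest imbalance this scheme allows. With seven blocks of 2:2, the arms at 28 are always 14:14.

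**The case against.** - **Equal allocation is assumed.** A deliberate 2:1:1 ratio would make blocks of 4 workable for the planned group, and a 2:1 ratio (10:5) would do so for blocks of 15 in the unplanned group, with 18 to 20 of the 28 in the larger arm. This stands as a limit: the ratio could be in Fig. 1. Nothing in the text supports either ratio.
- **A reader might infer that the printed sizes cannot give equal arms at all.** They can. In the planned group, rotating the doubled arm (five blocks for each) gives 5 × 2 + 10 × 1 = 20 per arm. In the unplanned group, 14:14 still arises in 40% of runs. What is true is narrower: no single block can be balanced. No rotating scheme is described.
- **That 28 is not a multiple of 15 is not an error by itself.** Recruitment need not stop at a block boundary, and the Safety monitoring plan allows termination before 88. This is right; the remainder only supports the inference of transposition.
- **The consequences are modest.** The main analyses are descriptive, and unequal arm sizes do not bias the estimates; they widen some intervals. This also stands.
- **A reader might infer that the wrong block sizes reached the drug supply.** The article does not show this. The trial statistician generates the codes, and neither the list nor protocol v3.1 is available here. The mistake may lie in this sentence alone.

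**Conclusion.** The concern holds in this form: under equal allocation, the block sizes in the Randomisation section fit neither group, and the two are very probably exchanged. The inconsistency follows from the article's own figures, and nothing elsewhere in it offers a correction. The transposition is an inference, supported by the exact fit of the exchanged sizes to both the arm counts and the totals.

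The effect, if the text was implemented, is conditional: up to a 15% larger standard error for one planned contrast under a fixed 2:1:1 block, and arms no worse than 16:12 in the unplanned group under randomly directed 8:7 blocks. The documents do not support saying that equal arms are impossible or that the list itself is wrong. They do show a stated allocation rule that should not stand uncorrected.

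**What to change.** 1. Check the generated randomisation list and the pack numbering at both sites against the intended design.
2. If equal allocation was intended, correct the sentence to blocks of 15 (5:5:5) for the planned group and blocks of 4 (2:2) for the unplanned group. If an unequal ratio was intended, state it and show that the block sizes fit it.
3. If packs are already in use, document the block sizes and ratio actually implemented. This is possible: the Trial status section aimed for recruitment by Spring 2016, and the article appeared in September 2016.

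The cost is one sentence and one check of the list, with no additional participants. Whether further work follows depends on what the check finds.

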**Fig. 1 Fig1:**
[figure not shown]
**a** CNWL Club Drug Clinic – Planned (outpatient) withdrawal, *N* = 60 (three groups). **b** GSTT clinical toxicology service – Unplanned (inpatient) withdrawal, *N* = 28 (two groups). *CNWL* Central North West London NHS Foundation Trust, *GSTT* Guy’s and St. Thomas’s NHS Foundation Trust

